#### Step 2a

Stress management, group format. Participants (6–8 patients/group) will meet for 2 hours every week for a total of 20 hours. In the intervals between the group meetings patients will be asked to do homework. This homework can entail practicing problem-solving techniques, keeping a diary, practicing relaxation or participating in physical activities. Each group meeting has a specific subject, derived from the 6 components in the intervention [24]. These components concern 1) basic knowledge about cancer, treatment, healthy living and stress reactions, 2) self-awareness with the help of a diary for thoughts, feelings and behavior, as well as group discussions of specific cases 3) instruction in various techniques about how to express negative feelings, how to communicate with others more effectively how to change behaviors related to stress, anger, worry and depression 4) training these techniques in real-life situations outside the group, 5) cognitive restructuring with the help of diaries, techniques and group dynamics and 6) spirituality, in a broad sense, with group discussions of quality of life, values, self-confidence and optimism. Written materials, case studies and video presentations will be used.

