The research group “Support project” has studied the effect of individual counselling conducted by a specially trained nurse [9]. This intervention was compared to the results of therapy conducted by a psychologist and to a group that received treatment as usual. The project started in 1997 with special training for nurses [10]. The project continued during for the next 5 years and data collection was concluded in January 2002. Patients in this study had been diagnosed with breast cancer and were offered adjuvant treatment. A total of 179 patients were consecutively included. The results showed that both active treatments had a positive effect, measured in terms of increased HRQoL and decreased symptoms of stress (e.g. intrusive thoughts) in comparison to the control group who received treatment as usual [9]. More patients in the control group took advantage of the psychosocial support that was available for all patients in standard care as compared to both intervention groups. The level of satisfaction was generally high in both intervention groups [11]. However patients in the nurse-counselor groups reported that greater satisfaction with interventions for worry, information about their illness, prognosis, tests, treatment as well as general contact with health care facilities than patients in the psychologist groups. Utilization of health care and number of days on sick leave can be attributed to the adjuvant treatment [12]. Both the intervention groups had lower total costs for medical care than the control group who required more days for in-patient care. The conclusions that can be drawn from this study are that the psychosocial interventions were useful for breast cancer patients, that they were relatively inexpensive and that interventions offered by nurses were as effective as those given by psychologists. The results of the “Support Project” described above generated additional questions. Most patients reported relatively high levels of HRQoL as well as relatively low levels of symptoms and side-effects of their illness and treatment. Despite these findings 75% of the patients reported that they had problems for which the psychosocial interventions provided help. A more detailed analysis of the data showed that 80% of the patients in the study reported a high level of stress symptoms initially, such as intrusive thoughts and avoidance behavior. These symptoms remained high throughout the study. Other symptoms such as worry and depression were also reported at high levels initially but these symptoms had decreased to normal levels after 3 months. This indicates that here is a need for closer examination of other factors for breast cancer patients, such as stress-related symptoms and behavior, predictors for stress, effects on role and social functions as well as utilization of heath care, sick leave and return to work settings. In addition there is a need to study how psychosocial interventions with a focus on stress management can influence the above-mentioned factors.

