### Intervention

All patients start at the first step of the intervention program and receive detailed information about different stress symptoms and different ways to deal with them. Patients will be given the opportunity to ask questions and will receive written material to be read at home. All patients are evaluated at the end of the intervention (Table 1) to see if they are clinically significant improved (CSI). CSI is defined as a decrease in stress related symptoms as measured by Impact of Event Scale (IES) and/or the Hospital and Depression Scale (HADS) from clinical levels to normal results. Patients who are evaluated as CSI as well as patients who did not report clinical levels on IES or HADS at the start of the intervention leave the program but are followed up during the coming year (Table 1). The remaining patients will be asked if they wish to continue in the program to the next step. Those patients who wish to continue will be randomised to group (Step 2a) or individual stress management (Step 2b). Within a week after randomisation patients will be contacted by telephone to receive information about which group they are assigned to and practical details about the start of the intervention.

**Table 1 T1:** Summary of interventions and measures used at repeated points in time

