### Data analysis

SPSS® ANOVA will be used to analyze differences between groups and for repeated measures over time for the continuous variables while nominal (categorical) variables will be tested with chi square (exact). Although not all the criteria for normal distribution are met by this selection the parametric tests are robust enough to be used. Patients’ levels of stress related symptoms will be categorized according to recognized cut-off points (See references in Table 1). A hierarchical linear regression analysis will be used to examine which variables predict stress symptoms and utilization of health care services as well as sick leave and return to work. Power calculations have been done for IES based on data from Support Project. On the basis of these conditions (power = 0.8, p = .05 and effect size = 0.59) at least 64 patients must be included in each group (i.e. a total of 128) patients) to detect a significant difference on IES.

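### The Step 2 comparison treats one arm in therapy groups of 6–8, but neither the named ANOVA nor the 64 per group allows for correlation within those groups

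*Protocol article*

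**What the plan says.** Under Intervention, patients who still have symptoms after Step 1 and wish to continue are individually randomised to group or individual stress management. Under Step 2a, the group arm is described as follows: "Participants (6–8 patients/group) will meet for 2 hours every week for a total of 20 hours". Interaction between members is part of the treatment; one listed component is "cognitive restructuring with the help of diaries, techniques and group dynamics". Under Step 2b, the same techniques are given in individual sessions.

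Under Data analysis, the method for continuous outcomes is: "SPSS® ANOVA will be used to analyze differences between groups and for repeated measures over time for the continuous variables". No term for therapy group is named. On sample size the section says "Power calculations have been done for IES based on data from Support Project", gives the inputs as "power = 0.8, p = .05 and effect size = 0.59", and concludes that "at least 64 patients must be included in each group (i.e. a total of 128) patients) to detect a significant difference on IES". No ICC or design effect is given. According to the Background, the group behind the Support Project "has studied the effect of individual counselling conducted by a specially trained nurse" and compared this with therapy by a psychologist and with usual care. No group format is mentioned there, so that study is not an evident source for a therapy-group correlation.

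**The concern.** Patients who share ten two-hour meetings (20 hours at 2 hours a week), the same discussions and the same fellow members are likely to have outcomes that resemble each other. Patients in the individual arm share no therapy group. The randomised comparison is therefore partially nested: 64 patients in the group arm form about 8 to 11 therapy groups (64/8 = 8; 64/6 = 10.7), and the other arm has none.

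An ANOVA on independent patients counts 64 separate pieces of information in the group arm when there are effectively fewer. Its standard error is then too small, its confidence interval too narrow and its p-value too low. A larger sample does not cure this.

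Group versus individual is the only randomised comparison in the trial, because everyone receives Step 1 and there is no control group. It concerns the primary outcome (IES), and the same problem affects the other patient-level continuous outcomes in that comparison.

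**Working it through.** **Inputs.** From Data analysis: effect size d = 0.59 in SD units, power 0.80, alpha 0.05 (two-sided assumed; the document does not say), n = 64 per arm. From Step 2a: group size m = 6–8, with 7 as midpoint. Assumed, because the document gives none: ICC from 0.01 to 0.20. Equal total variance in both arms is also assumed.

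**1. The plan's own figure.** For independent patients, n per arm = 2 × ((1.960 + 0.842)/d)².
- d = 0.59: 2 × (2.802/0.59)² = 45.1, so 46 (47 with the t-test; 36–37 if one-sided).
- d = 0.50: 2 × (2.802/0.50)² = 62.8, so 63 (64 with the t-test).

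The stated 64 does not follow from the stated 0.59 at 80% power. It matches d = 0.50. With d = 0.59 and 64 per arm, power is 91.6% (t-test 91.2%). Going from 47 to 64 would need a dropout allowance of 1 − 47/64 = 27%, and none is stated.

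**2. Effect of ignoring therapy groups.** Design effect in the group arm only: DE = 1 + (m − 1) × ICC. True variance of the difference relative to the naive one: R = (DE + 1)/2. Type I error of the naive test: 2 × (1 − Φ(1.960/√R)). Power: Φ(d × √(32/R) − 1.960) at 64 per arm. For m = 7:

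| ICC | DE | R | true SE / naive SE | naive type I error | power, d = 0.59 | power, d = 0.50 |
|---|---|---|---|---|---|---|
| 0 | 1.00 | 1.00 | 1.00 | 5.0% | 91.6% | 80.7% |
| 0.01 | 1.06 | 1.03 | 1.015 | 5.35% | 90.8% | 79.6% |
| 0.05 | 1.30 | 1.15 | 1.07 | 6.8% | 87.5% | 75.1% |
| 0.10 | 1.60 | 1.30 | 1.14 | 8.6% | 83.3% | 69.9% |
| 0.20 | 2.20 | 1.60 | 1.26 | 12.1% | 75.1% | 60.9% |

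The power columns refer to an analysis that uses the correct standard error.

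**3. Few therapy groups.** With k = 64/7 = 9.1 groups, the Satterthwaite degrees of freedom are (DE + 1)² / (DE²/(k − 1) + 1/63).
- ICC 0.05: 2.3²/(1.69/8.14 + 0.016) = 23.7.
- ICC 0.10: 2.6²/(2.56/8.14 + 0.016) = 20.5.

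The naive test uses 126. With these degrees of freedom (noncentral t), power is 84.7% and 79.6% at d = 0.59, and 71.6% and 65.7% at d = 0.50.

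**4. Where 80% is lost if d = 0.59.** Setting power to 80% gives DE + 1 = 64 × 0.59²/2.802² = 2.84, so DE = 1.84. At m = 7 the ICC is 0.84/6 = 0.14 (0.17 at m = 6, 0.12 at m = 8). With the degrees of freedom from step 3, the threshold at m = 7 drops to about 0.10.

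**5. Simulation check.** Nine groups of 7 against 63 individual patients, 20,000 runs. The naive t-test rejected a true null in 6.8%, 8.3% and 12.6% of runs at ICC 0.05, 0.10 and 0.20. A test based on therapy-group means held 5.0% at both 0.05 and 0.10. At d = 0.59 that test had power 84% and 78%.

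**The case against.** **The stated 80% power.** A reader might infer that ignoring clustering means the claimed 80% power is overstated. The document does not support that. On its own inputs the unclustered power is about 91%, and this slack absorbs clustering up to an ICC of roughly 0.10–0.14 at 7 per group. A fall from 80% to 72–75% requires an effect size of 0.50, which appears nowhere in the article. It may lie behind the 64, but that is a conjecture. This part of the objection stands in full.

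**The unknown ICC.** The size of the inflation rests on an assumption. At 0.01 it is negligible, and the degrees of freedom of 20–24 apply only at ICC 0.05–0.10. This stands as a limit on the size. The direction does not depend on the value, provided the ICC is positive, and a treatment that relies on group dynamics makes zero hard to presume.

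**A condensed article.** ANOVA can carry a nested random factor, and a fuller analysis plan might specify one. But the article does state a test and a sample size, and neither as written allows for therapy groups. Its one remark on assumptions concerns normality, and robustness to non-normality does not cover dependence between patients.

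**Scope and slack.** Only the Step 2 comparison is affected; the Step 1, prevalence and prediction aims are not. The Design section expects about 150 patients eligible for Step 2. At 75 per arm, power by the step 2 formula would be 92% and 89% for d = 0.59 at ICC 0.05 and 0.10. That is helpful but not assured, because entry depends on patients wishing to continue, and it does nothing for type I error.

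**Nurses.** Nurses deliver both formats, so the individual arm could be clustered by nurse. This is a fair supplement to the remedy, not a reason to ignore therapy groups.

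**Conclusion.** The concern holds for the analysis and, in a limited form, for power.

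If the Step 2 comparison is analysed as written and the ICC is positive, its standard error is too small by a factor of about 1.07 at ICC 0.05 and 1.14 at ICC 0.10. Its nominal 5% test then has a true level of about 6.8% and 8.6%. At ICC 0.01 the level is about 5.35%, which would not matter in practice. These figures assume 7 per group, equal total variance, 64 per arm and a two-sided test.

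Power is lower than for independent patients, but by how much cannot be settled until the stated 0.59 is reconciled with the stated 64. If 0.59 is right, power is about 85–88% at ICC 0.05 and 80–83% at ICC 0.10. If the basis was about 0.50, it is about 72–75% and 66–70%. The finding is therefore not that the stated 80% is missed, but that the design and the named analysis leave out a source of variation in the trial's only randomised comparison.

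**What to change.** 1. Record a therapy-group number for every Step 2a patient while the groups run. Data collection provides for recording attendance at sessions but names no group identifier, and it may be hard to reconstruct later.
2. Replace the ANOVA for the Step 2 comparison with a partially nested linear mixed model: a random therapy-group effect in the group arm, arm-specific residual variance, and Satterthwaite or Kenward-Roger degrees of freedom. Where several time points are modelled, keep the within-patient correlation as well. If the treating nurse is recorded, a sensitivity analysis by nurse can be added.
3. State which effect size the 64 per group rests on, and correct whichever of 0.59 and 64 is wrong. Then restate power over a declared ICC range, for example 0.01 to 0.10, with the design effect applied to the group arm. Enrolment need not change.

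The cost is one extra variable, a mixed model that the same software can fit, slightly wider intervals and a more cautious power statement. With only about 8 to 11 therapy groups, the small-sample degrees of freedom cost a little power even when the ICC is near zero.

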### Step 2b Individual intervention

The methods and techniques will be the same as those used in the group intervention. The first session will be used for a detailed assessment of the individual’s psychosocial problems, as used in earlier studies [9,11]. The sessions will last 45–60 minutes. The number of sessions will depend on the individual patient’s problems and the joint assessment made by the patient and nurse together. The total number of sessions will be at least 4, with a maximum of 8. The contents of the sessions are Session 1: Assessment, Session 2: Analysis of diary (self-registration) and suggestions for problem management, Session 3: Evaluation of problem management skills Session 4: Follow-up and conclusion of the intervention. When necessary Sessions 5–8 will address specific obstacles and continued practice.

### Implementation

Patients will receive written information about the project when they receive notice for a doctor’s appointment to discuss adjuvant treatment for breast cancer. They will be asked if they wish to participate in the project for stress management by their doctor or by a member of the project group after the appointment. If they answer “yes” they will then receive the first set of questionnaires. Their answers constitute the baseline measures as well as a prevalence screening for stress symptoms. When the questionnaires are completed the patient will receive a written invitation to Step 1 of the intervention program, i.e. to a lecture on stress management. The intervention program will take place in Falun, Gävle or Uppsala, and be conducted by specially trained nurses who will receive continual supervision. The nurses who conduct the intervention program will be trained in general stress management, psychosocial oncology as well as assessment and treatment of psychosocial problems.

### Data collection

Data will be collected by use of well-known questionnaires. An outline of the assessment points and questionnaires are included in Table 1. When patients are included in the study, they were mailed the baseline questionnaires, which included a signed consent to participate and a prepaid envelope. Later measurements will be sent out to the patients’ homes, together with a stamped, pre-addressed envelope. Patients who have not returned the completed questionnaires after 14 days will be contacted by telephone by a member of the project staff to insure as high a response rate as possible. Information about the patients’ demographic and medical background will be obtained from their medical records. Utilization of hospital services will be collected from the hospitals’ computer systems. Information about utilization of other professional care facilities will be collected from patients’ self-reports. Sick-leave information will also be collected by self-report. The nurse-counsellor will record attendance at individual and group sessions.

### Data analysis

SPSS® ANOVA will be used to analyze differences between groups and for repeated measures over time for the continuous variables while nominal (categorical) variables will be tested with chi square (exact). Although not all the criteria for normal distribution are met by this selection the parametric tests are robust enough to be used. Patients’ levels of stress related symptoms will be categorized according to recognized cut-off points (See references in Table 1). A hierarchical linear regression analysis will be used to examine which variables predict stress symptoms and utilization of health care services as well as sick leave and return to work. Power calculations have been done for IES based on data from Support Project. On the basis of these conditions (power = 0.8, p = .05 and effect size = 0.59) at least 64 patients must be included in each group (i.e. a total of 128) patients) to detect a significant difference on IES.

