## Background

A life threatening illness such as breast cancer can lead to a secondary diagnosis of PTSD (post traumatic stress disorder) [1]. The reported frequency of PTSD for breast cancer patients varies between 2–22%, depending on methods of measurement. At present it is therefore difficult to draw any conclusions about the actual prevalence of PTSD. Intrusive thoughts, avoidance behavior and worry are all common symptoms. Nordin and Glimelius [2] reported that clinical levels of worry or depression in combination with intrusive thoughts in individuals with breast cancer make it possible to identify women who will need psychological support at a later stage of treatment. In a study [3] it was found that measures of avoidance behavior could predict the effects of treatment on an individual’s quality of life. Extensive avoidance behavior at the start of treatment is correlated with deterioration in physical and social functioning as well as impaired general health. Half of the women diagnosed with breast cancer in Sweden are under the age of 65 and at least theoretically gainfully employed [4]. To juggle the demands of work and a family, especially when there are children living at home, is a demanding task [5]. To be diagnosed with breast cancer on top of these demands can be the straw that breaks the camel’s back. At present there is very little research that has examined this combination of stress factors in women diagnosed with breast cancer.

In an international perspective there is a fair amount of evidence which indicates that methods which are based on cognitive behavior therapy can improve health-related quality of life (HRQoL), reduce psychosocial stress and increase perceived Personal control of treatment side-effects and disease symptoms for cancer patients [6,7]. According to SBU (The Swedish Council on Technology Assessment in Health Care) providing cognitive behavior therapy 1–3 months after a traumatic event reduces the occurrence of PTSD in states of intensive stress [8]. At present there is a lack of solid research findings for comparisons of cost-effectiveness and outcome [8].

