### Design

The study is a prospective longitudinal intervention study with a stepped-care approach [13], where patients will be randomised to one of two interventions in the final stage of treatment. One of the key concepts in the stepped-care model is that the needs of the individual are matched to the appropriate level of care [13]. The first step is a low intensity intervention that is given to all patients. Patients who do not respond to this level are thereafter given more intensive treatment at later steps in the program. Since methods from CBT (cognitive behavior therapy) have already been shown not only to reduce the risk for PTSD [8] but also to have a positive effect on quality of life and psychological well being for patients with breast cancer [9,14], there is no control group in the study. All patients (n = 300) will receive the first level of the intervention program. All patients (estimated to n = 150) who continue to report stress symptoms after the first step of the intervention program will be given the chance to participate in the second step of the program. The second step includes randomisation to one of two treatments: a stress management group or individual stress management (See Figure 1). With this design it will be possible to study the prevalence of stress related symptoms as well as to study which factors predict which patients will be Clinically Significant Improved (CSI) with a basic level of education about stress management. In addition the study will help to identify those patients who need additional help and to compare the effects of individual and group interventions.

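### Linear regression is named for return to work, which is a yes/no or censored outcome, and for sick leave and service use, which are likely skewed

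*Protocol article*

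**What the plan says.** The Data analysis section gives one regression method for all predictor questions: "A hierarchical linear regression analysis will be used to examine which variables predict stress symptoms and utilization of health care services", continuing "as well as sick leave and return to work". Earlier in the same section, ANOVA is assigned to continuous variables and an exact chi-square test to categorical ones, followed by: "Although not all the criteria for normal distribution are met by this selection the parametric tests are robust enough to be used".

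The Design section adds a further prediction aim: the design allows the investigators to study "which factors predict which patients will be Clinically Significant Improved (CSI") with the basic step. The Intervention section defines clinically significant improvement (CSI) as a fall on the IES and/or HADS "from clinical levels to normal results". It treats "patients who did not report clinical levels on IES or HADS at the start of the intervention" as a separate category; they leave the programme alongside the improved patients and are followed up. CSI does not appear in the list of regression outcomes.

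Table 1 collects self-reported sick leave at inclusion, at 3 months, and at 1 and 12 months after completed intervention. The article does not define the return-to-work variable, but the Discussion names a quicker return as one of the hoped-for gains.

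**The concern.** A condensed article may leave detail to a fuller plan. Here, however, a model is named and its outcomes are listed, and for at least one of them the model is a poor match.

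Return to work is a status or a time to an event. Follow-up stops at the last questionnaire, so some women may not yet have returned, and a linear model cannot represent that. Sick leave and service use have a floor at zero and probably a long upper tail, so a constant additive effect may describe them badly.

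At stake is the size of the effects reported for predictors of work and service-use outcomes, which the Discussion presents as important benefits. The randomised comparison on the IES does not depend on these models.

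**Working it through.** The article gives no figure for these analyses, so there is none to reproduce. The check sets outcomes against model and then gauges the consequence.

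**Step 1. Outcome against model (Data analysis, Design, Intervention).**

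| Outcome | Natural scale | Model named | Fit |
|---|---|---|---|
| Stress symptoms as IES or HADS scores | Continuous | Hierarchical linear | Suitable |
| Return to work | Yes/no, or time with censoring | Hierarchical linear | Poor |
| Sick leave, service use | Non-negative, likely skewed | Hierarchical linear | Weak |
| CSI | Yes/no | No regression named | Aim without a matching model |

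**Step 2. Return to work read as a time.** Let T be the time to return and C the time of the last assessment. For a woman still off work, only T > C is known. A linear model leaves two choices:
- Drop her. The analysis then estimates the mean of T given T ≤ C, which is below the mean of T and removes the slowest returners.
- Enter Y = min(T, C). A predictor that delays return from just after C to long after C leaves Y unchanged, so part of its effect is lost.

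**Step 3. Return to work read as yes/no.** The variance of a binary outcome is p(1 − p): 0.1 × 0.9 = 0.09 at 10% and 0.5 × 0.5 = 0.25 at 50%, a ratio of 0.25/0.09 = 2.8. The constant variance assumed by ordinary least squares therefore fails when risk varies with the predictors. This shows unequal variance; it does not measure any error in interval width.

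**Step 4. Simulation of ordinary least squares on a yes/no outcome.** Assumptions, none from the article except the sample sizes: one standard normal predictor, 1,000 data sets per setting, N = 300 (all patients) or 150 (the Step 2 estimate), probability 0.5, 0.8 or 0.9 at the predictor mean, odds ratio 2 or 3 per SD. Type I error was obtained with an outcome unrelated to the predictor.

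| Probability | Odds ratio | Fits outside 0–1, N = 300 | Fits outside 0–1, N = 150 |
|---|---|---|---|
| 0.5 | 2 | 0.3% | 0.5% |
| 0.5 | 3 | 2.6% | 2.8% |
| 0.8 | 2 | 2.7% | 3.0% |
| 0.8 | 3 | 7.5% | 7.5% |
| 0.9 | 2 | 4.8% | 5.3% |
| 0.9 | 3 | 11.0% | 11.3% |

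Type I error lay between 0.037 and 0.062. Simulation error alone gives 0.05 ± 1.96 × √(0.05 × 0.95/1000) = 0.05 ± 0.014, that is 0.036 to 0.064, so no departure from 5% is visible.

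**Step 5. Skewed outcome.** Assumptions: N = 300, 40% zeros, otherwise log-normal with log-SD 1 and a log-mean of 3.5 that rises by 0.5 per SD of the predictor. About 2.7% of fitted values were negative. Type I error without a predictor effect was 0.044.

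**Limits.** Neither simulation includes censoring, the main difficulty for return to work. Under the null with a single predictor the residual variance is constant, so these type I results come from a favourable case.

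**Step 6. CSI.** CSI requires a clinical level at the start and a normal one afterwards. A patient without a clinical level at the start has probability zero of CSI by definition. Counting her as a failure would make a low starting score look like a predictor of not improving.

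**The case against.** The strongest reply is that these are secondary, exploratory analyses meant to find which variables predict, not to issue individual predictions, and that tests from a linear model held their level in simulation. Return to work is also undefined, so a continuous measure cannot be excluded. The point about tests stands, and it limits the harm to estimates and fitted values. The point about definition does not rescue the model, because a measure such as days until return would still be censored.

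A reader might infer more than the article supports:
- **That linear regression is assigned to CSI.** It is not. Chi-square and ANOVA can test single predictors, and a fuller plan may hold a multivariable model. This part is a gap between aim and described analysis, not a stated error.
- **That about half the patients are the wrong ones for work outcomes.** The Background says "Half of the women diagnosed with breast cancer in Sweden are under the age of 65 and at least theoretically gainfully employed", and 0.5 × 300 = 150. That is a national figure, not a trial figure, and nothing says that retired women enter these analyses.
- **That service use and sick leave are full of zeros.** This is not documented. All patients are scheduled for adjuvant treatment, and the Background links health-care use and sick leave in the earlier study to that treatment, so many zeros in hospital contacts are unlikely. Skew remains plausible. The 40% in Step 5 is only an assumption.
- **That the robustness sentence defends the regressions.** It follows the ANOVA and chi-square sentence, precedes the regression and speaks of tests. At most it answers non-normality, not censoring or a yes/no scale.
- **That confidence intervals are shown to have the wrong width.** No calculation here shows that.

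**Conclusion.** The point holds in a limited form. The named linear model fits return to work badly under either natural reading, and fits sick leave and service use less well than available alternatives. It is appropriate for continuous stress scores.

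The effect is on estimated effects and fitted values: 0.3% to 11% of fitted probabilities out of range, worst at a probability of 0.9 and an odds ratio of 3, and about 2.7% negative fits for a skewed outcome. All of these rest on the simulation assumptions. The loss from censoring cannot be sized, because the article does not say how many women are expected to be off work at the last assessment.

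The primary IES outcome, the randomised comparison and the sample size are untouched. The change is worth making before analysis because it is cheap.

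**What to change.** Reword the regression sentence so that the model follows the outcome:
- **Stress symptoms:** keep hierarchical linear regression for continuous IES and HADS scores.
- **Return to work:** use hierarchical logistic regression for status at one stated assessment, in women working at diagnosis. Use Cox regression, censored at last follow-up, only if return dates are recorded; the article describes self-report at a few assessments and shows no dates.
- **Sick-leave days and service contacts:** use a count model such as negative binomial, or linear regression with robust or bootstrap standard errors. Restrict sick leave to women working at diagnosis as well.
- **CSI:** use logistic regression on variables measured at inclusion, restricted to patients with clinical IES or HADS levels at the start.

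The cost is a smaller n for the work outcomes and for CSI, and slightly more analysis work with standard procedures. Employment at diagnosis must be known; if it is not already among the background data taken at inclusion, one item has to be added. Design, interventions and sample size stay as they are.
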